### Biobank

A biobank will be established at the Laboratory Center, Vejle Hospital for translational research.

The remaining material will be stored for 10 years in a biobank for future research and then destroyed. The biobank is approved by The Region of Southern Denmark.

### Statistical analysis and sample size

The present study will compare the treatment outcomes of patients in the two arms.

Based on previous studies we expect an OIPN prevalence of 50% in the control group and estimate a prevalence in the fish oil group to be 23%, which is a clinically meaningful difference [6, 39, 63]. Using 80% power and 5% risk of type I error, the sample size estimate is 49+49 patients for the primary objective. To account for dropouts, the project will include 120 patients, with 60 patients in each group.

Patient demographics and baseline characteristics will be described using descriptive statistics. Continuous variables will be summarized according to their distribution with medians and interquartile range (IQR) or means and standard deviations (sd). Categorical variables will be summarized with frequencies and percentages.

The primary endpoint (OIPN) is a dichotomous endpoint defined by the developed definition of OIPN. The two independent proportions of OIPN in the two randomization arms will be compared using the chi^2^ test and reported as frequencies and percentages with corresponding p-values. P-values <0.05 will be considered statistically significant. All analyses will be performed as intention-to-treat (ITT). In case of cross-over between study arms due to non-compliance, per protocol analyses will be performed as sensitivity analyses to explore the potential bias from the non-compliance. In per-protocol analyses, non-compliance will be defined using an 80% percent cut-off or a significant lack of DHA and EPA rise in compliance blood samples.

The proportion and patterns of missing data will be explored, and in the case of <5% missing data, analyses will be performed as complete case. If the amount of missing data is comprehensive (>5%) or suggestive of biased estimates, appropriate methods of imputation will be applied depending on the patterns of missingness.

A complete statistical analysis plan covering each outcome will be developed together with statistical consultant [name] M.Sc., PhD. Statistical analyses will be performed using STATA version 18 (STATA Corp., Texas, USA) and all steps of data management, coding and analyses will be logged.

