### Study population and eligibility

Patients diagnosed with colorectal cancer, operated, and referred to one of four participating Departments of Oncology at University Hospital of Southern Denmark Vejle, University Hospital of Southern Denmark Soenderborg, Aarhus University Hospital, and Aalborg University Hospital are eligible. Patients meeting the inclusion criteria (Table 1) will be invited to participate and provide written informed consent.

**Table 1 Tab1:** Inclusion and exclusion criteria

Inclusion criteria	Exclusion criteria
• Histopathologically verified adenocarcinoma of the colon or rectum and planned standard adjuvant treatment with capecitabine in combination with oxaliplatin • Age ≥ 18 • ECOG performance status 0-2 (measurement of a patient’s function in terms of self-care, daily activity and physical ability) [46] • Written and orally informed consent.	• Inability to speak, read, and understand Danish • Previous treatment with neurotoxic chemotherapy • Neurological (including neuropathy) or psychiatric disorders, diabetes, or other significant medical conditions • Alcohol or drug abuse • Sensory disturbances in the feet • Spinal stenosis • Vascular disease (Fontaine grade II or more) • Known allergy to fish, fish oil or corn oil • Fertile patients not willing to use effective methods of contraception during treatment or abstinence • Daily intake of oil supplements and not willing to stop during the trial period • Lack of consent to skin biopsy

ECOG: Eastern Cooperative Oncology Group

Dietary intake of LCPUFAs in the Danish population is low and thus not expected to affect the trial. Therefore, dietary intake is not documented, and specific diets are not cause for exclusion [47, 48].

If patients experience verified disease relapse, they will be withdrawn from the trial. Dose reduction or premature cessation of oxaliplatin is not cause for exclusion if the patient has received at least one dose of oxaliplatin.

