### Randomization and blinding

Randomization is carried out automatically 1:1 and stratified to the study site via the Research Electronic Data Capture (REDcap) randomization module and is fully blinded (patient, health care provider, investigator). In case of a medical emergency and proper treatment requires knowledge of the treatment randomization, unblinding is possible via the hospital pharmacy which has randomization envelopes. At the end of the trial period and subsequent data analysis, unblinding will take place.

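### Randomisation is stratified by site but the primary chi-square test ignores site; a site-stratified test is a nearly free, modest improvement

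*Protocol article*

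**What the plan says.** Under Randomization and blinding: "Randomization is carried out automatically 1:1 and stratified to the study site". Under Study population and eligibility, patients are those "referred to one of four participating Departments of Oncology", so there are four strata.

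Statistical analysis and sample size treats the primary endpoint (OIPN at 8 months, yes or no) as two independent proportions that "will be compared using the chi^2^ test and reported as frequencies and percentages with corresponding p-values", with significance at p below 0.05. Site is not mentioned.

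The same section gives the planning figures: "we expect an OIPN prevalence of 50% in the control group", "estimate a prevalence in the fish oil group to be 23" (percent), "Using 80% power and 5% risk of type I error", and "the sample size estimate is 49+49 patients for the primary objective". After allowance for dropout, "the project will include 120 patients, with 60 patients in each group". It also announces a full statistical analysis plan for each outcome, which is not at hand.

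**The concern.** Stratified allocation balances the arms within each site, so differences in prevalence between sites largely cancel out of the arm comparison. The plain chi-square test computes its variance as if that balancing had not been done, so the between-site part stays in the standard error. If sites differ, the standard error is too large, the true type I error falls below nominal, and power is left unused.

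Some site difference is possible. The symptom part of the endpoint is judged by a medical professional, two of the supporting tests (tuning fork and pinprick) are bedside tests, and the sites open at different times between June 2022 and a planned October 2023.

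What is at stake is efficiency, not validity. The announced analysis plan does not remove the point, because the article already names the primary test; a plan that follows it would carry the mismatch forward.

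**Working it through.** **Inputs from the article.** Control 50%, fish oil 23%, 80% power, 5% alpha, 49 per arm evaluable, 60 per arm enrolled, four sites, 1:1 within site. Sidedness is not stated; two-sided is assumed and reproduces the stated number.

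**Step 1: the plan's own figure.** With pooled variance, no continuity correction and mean prevalence (0.50 + 0.23)/2 = 0.365:

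n = [1.960 × √(2 × 0.365 × 0.635) + 0.842 × √(0.50 × 0.50 + 0.23 × 0.77)]² / 0.27²
= (1.334 + 0.550)² / 0.0729 = 48.7, rounded up to 49 per arm.

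This matches. Power by the same formula is 80.2% at 49 per arm and 87.7% at 60. The sample size and the named test therefore agree with each other.

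**Step 2: why the test is conservative.** Under no treatment effect and overall prevalence 0.50, the chi-square test uses variance 0.50 × 0.50 = 0.25 per patient. With balance within sites, the variance that applies is 0.25 minus the variance of the site prevalences. Take an assumed 30-70% spread with sites at 0.30, 0.43, 0.57 and 0.70:

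- Between-site variance = (0.04 + 0.0049 + 0.0049 + 0.04)/4 = 0.0225.
- Ratio of true to assumed variance = 1 − 0.0225/0.25 = 0.91.
- The nominal cut-off of 1.96 acts like 1.96/√0.91 = 2.05, a large-sample type I error of about 4.0%.

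Simulation gives 4.4%. Discreteness at this sample size raises it a little; the same effect puts both tests at about 5.4% when sites are identical.

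**Step 3: simulated size of the effect.** Four near-equal sites, arms balanced within site, common odds ratio across sites, and overall arm rates held at the planned 50% and 23%. The site spreads are assumptions. Results at 49 per arm:

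| Control prevalence across sites | Chi-square power | CMH power | Gain (points) | Chi-square type I error |
|---|---|---|---|---|
| 50% at all sites | 80.1% | 80.2% | 0.1 | 5.4% |
| 40-60% | 80.4% | 80.9% | 0.5 | 5.2% |
| 30-70% | 81.2% | 83.5% | 2.3 | 4.4% |
| 20-80% (extreme) | 82.5% | 87.7% | 5.2 | 3.1% |

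The CMH type I error stays between about 4.9% and 5.5%. At 60 per arm the pattern is the same, in the same order: 87.7% versus 87.5%, 88.0% versus 88.2%, 88.7% versus 90.3%, and 90.0% versus 93.4%. Unequal sites (4:3:2:1) give similar results.

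**The case against.** The case for leaving the test alone is fair in several respects. The error is on the safe side, the sample size was computed for this same test, and no site prevalences are documented. All four sites are Danish oncology departments with one eligibility list, and the endpoint also requires an abnormal result on a test with specified methods, which limits drift between sites. A 20-80% range is hard to believe, and at 40-60% the gain is about half a point. All of this stands and keeps the point modest. It does not argue for the unstratified test, because the stratified one costs almost nothing when sites are alike.

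Two stronger readings are tempting but not supported.

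- **That ignoring site leaves the trial underpowered.** If the odds ratio is fixed at (0.23/0.77)/(0.50/0.50) = 0.299 and sites are spread, chi-square power does drop: to roughly 73-75% at 30-70% and 65% at 20-80%. But the average fish-oil prevalence then becomes 24.8% and 27.2%, so most of the drop reflects a smaller overall effect than planned. The stratified test falls too, to about 77% and 73%. The article plans overall rates of 50% and 23%; with those held, chi-square stays above 80%. Only the gap between the two tests is the cost of ignoring site.
- **That the primary result will be a bare p-value.** The article also promises frequencies and percentages by arm, from which a crude difference can be derived. No effect measure or confidence interval is named, but that may be left to the announced analysis plan and is not a fault of the article.

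**Conclusion.** The point holds as a mismatch between design and analysis with a modest cost. The article stratifies by site and then fixes a primary test that ignores site. Relative to a stratified test, the forgone power at 49 per arm is about 0.5 points for a 40-60% site spread, 2.3 for 30-70% and 5.2 for 20-80%, and essentially nil if sites do not differ. Type I error is not inflated by site differences, and 49+49 needs no revision.

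These sizes rest on assumed site prevalences, a common odds ratio across sites, balance within sites, and the planned overall rates. The direction does not depend on the particular spread chosen; the size does.

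**What to change.** Before unblinding, state in the analysis plan that the primary test is a Cochran-Mantel-Haenszel test stratified by study site. Report the Mantel-Haenszel risk difference with its 95% CI next to the frequencies, percentages and p-value already planned, and keep the plain chi-square as a supportive analysis.

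The interval is worth having. If the planning rates were observed at 49 per arm, the crude Wald interval would be 27 ± 1.96 × √[(0.25 + 0.1771)/49] × 100, or about 8.7 to 45.3 points.

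The cost is a sentence or two of wording. No new data, patients or sample size calculation are needed. If sites turn out alike, the two tests differ by at most about 0.2 points of power (80.1% versus 80.2% at 49 per arm, 87.7% versus 87.5% at 60).

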### Intervention

Intervention capsules consist of fish oil containing 500 mg EPA, 20:5n-3 and 250 mg DHA, 22:6n-3 each. A daily dose of four capsules will supply 2 g EPA and 1 g DHA. The control capsules consist of 1 g corn oil of which 52% is PUFA n-6. The daily control dose of four capsule is 2.08 g n-6 PUFA (linoleic acid) The corn oil dosage is equivalent to normal dietary intake and has no known effect on the examined parameters.

Intake of active or control capsules continues until 8 months after enrollment. No titration or tapering off is needed.

Active and control capsules are manufactured by EPAX Norway a/s (Aalesund, Norway). Monitoring of durability and verification of content in supplied capsules will be carried out by the supplying company EPAX. Capsules are labeled by the hospital pharmacy Vejle Hospital, according to Eudralex - Volume 4, Annex 13.

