### Compliance

Compliance will be monitored continuously through verification and registration by a study nurse at each visit. The excess capsules will be counted, and patients will be asked about their compliance at each visit. During the trial two phone calls will be placed with the purpose of compliance and patient retention.

Furthermore, in a subgroup, we will evaluate compliance in blood samples taken at three different time points (visits 1, 4 and 5, see Fig. 1). The n-3 LCPUFA content in erythrocyte membrane is measured as an objective measure of compliance. The samples will be analyzed by high-throughput fatty acid analysis by gas chromatography with flame ionization detection using Varian 3900 or Agilent 7890A instruments [49]. Samples are stored and shipped in bulk for analysis at the Laboratory of Nutritional Lipidomics, Department of Kinesiology and Health Sciences, Faculty of Health, University of Waterloo, Canada.

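### The per-protocol compliance rule names no arm: it rejects blood-sampled compliant corn-oil patients and has no test for a control who also takes fish oil

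*Protocol article*

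**What the plan says.** In the protocol article, *Statistical analysis and sample size* makes intention-to-treat the basis of all analyses and adds a conditional one: "In case of cross-over between study arms due to non-compliance, per protocol analyses will be performed as sensitivity analyses". For that analysis, "non-compliance will be defined using an 80% percent cut-off or a significant lack of DHA and EPA rise in compliance blood samples". The two criteria are joined by an or, so meeting either one makes a patient non-compliant, and neither is tied to an arm.

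*Compliance* describes the measurements. Leftover capsules are counted and patients are questioned at each visit. In addition, "in a subgroup, we will evaluate compliance in blood samples taken at three different time points" (visits 1, 4 and 5), and "The n-3 LCPUFA content in erythrocyte membrane is measured as an objective measure of compliance". The size of the subgroup is not given.

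*Intervention* gives the contents. For fish oil, "A daily dose of four capsules will supply 2 g EPA and 1 g DHA". For the comparator, "The control capsules consist of 1 g corn oil of which 52% is PUFA n-6"; no EPA or DHA is listed. *Study population and eligibility* adds that "Dietary intake of LCPUFAs in the Danish population is low and thus not expected to affect the trial", and excludes daily users of oil supplements who will not stop. The *Discussion* justifies the blood measure by the fact that anyone can buy fish oil in ordinary shops.

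**The concern.** A rise in EPA and DHA means opposite things in the two arms. In the fish-oil arm it shows that the capsules were taken. In the corn-oil arm it shows that the patient obtained n-3 fatty acids elsewhere. A single criterion based on a lack of rise therefore cannot serve both arms.

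The per-protocol analysis is meant to explore bias from non-compliance and cross-over. If its set drops compliant controls and keeps contaminated ones, the control group moves towards the active condition. If the criterion is confined to fish oil, that arm is cleaned more strictly than the other. Patients who adhere poorly may differ in neuropathy risk, so uneven exclusion can create a difference where there is none. Either way, the analysis could mislead on the question it was added to answer.

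**Working it through.** **The plan's own figure.** With 50% versus 23%, two-sided 5% and 80% power, the pooled two-proportion formula gives n = [1.96·√(2·0.365·0.635) + 0.842·√(0.25 + 0.1771)]² / 0.27² ≈ 48.7, so 49 per arm as stated. The point below does not dispute it.

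**Classification under the rule as written**, for blood-sampled patients, taking the 80% to mean capsules taken:

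| Patient | 80% criterion | Lack-of-rise criterion | Result |
|---|---|---|---|
| Fish oil, takes capsules | passes | passes | kept, rightly |
| Fish oil, does not take capsules | fails if count is accurate | fails | removed, rightly |
| Corn oil, takes capsules only | passes | fails | removed, wrongly |
| Corn oil, takes capsules plus bought fish oil | passes | passes | kept, wrongly |
| Corn oil, replaces capsules with bought fish oil | fails | passes | removed, as missed capsules |

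**Size if the rule is applied to both arms.** Inputs from the protocol: 60 per arm; risks of 50% and 23%. Assumed: tested share s; a fraction c of controls taking bought fish oil on top of the trial capsules, at risk 23%; everyone compliant by capsule count.

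- Controls retained = 60·[(1 − s) + s·c].
- Contaminated share of those retained, x = c / [(1 − s) + s·c].
- Expected control risk = 0.50·(1 − x) + 0.23·x.

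| s | Retained, c = 0 | Retained, c = 10% | x, c = 10% | Control risk, c = 10% |
|---|---|---|---|---|
| 25% | 45 | 46.5 | 13% | 46.5% |
| 50% | 30 | 33 | 18% | 45.1% |
| 75% | 15 | 19.5 | 31% | 41.7% |
| 100% | 0 | 6 | 100% | 23% |

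Without the blood criterion, x would be 10% and the control risk 0.9·0.50 + 0.1·0.23 = 47.3%. The rule concentrates the contamination.

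**Size if the rule is read as fish-oil only.** Contaminated controls stay, so x remains 10% in the example. For the uneven exclusion, assume no treatment effect, 50% overall risk and 20% non-adherers in each arm. Two risk patterns are consistent with this:

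- A: adherers 47.5%, non-adherers 60% (0.8·47.5 + 0.2·60 = 50).
- B: adherers 45%, non-adherers 70% (0.8·45 + 0.2·70 = 50).

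*Upper bound:* all non-adherers leave the fish-oil arm and none leave the control arm. The spurious benefit is 50 − 47.5 = 2.5 points (A) or 50 − 45 = 5 points (B).

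*With the 80% cut-off acting in both arms:* suppose it catches half of the non-adherers in each arm, half of all patients are tested, and the blood test finds the rest among those tested. Per 100 randomised, controls keep 80 adherers and 10 non-adherers; fish oil keeps 80 and 5.

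- A: control (80·0.475 + 10·0.60)/90 = 48.9%; fish oil (80·0.475 + 5·0.60)/85 = 48.2%; difference about 0.7 points.
- B: control (80·0.45 + 10·0.70)/90 = 47.8%; fish oil (80·0.45 + 5·0.70)/85 = 46.5%; difference about 1.3 points.

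**The case against.** The strongest reply is that a lack of rise only makes sense where a rise is expected, so the authors must have meant the fish-oil arm. That is plausible, but the text does not say so. Even on that reading, the rule has no criterion for a rise in a control, and it subjects tested fish-oil patients to an exclusion that controls do not face.

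A second reply is that the rule does catch some cross-over, and this stands. A fish-oil patient who stops the capsules is detected by the blood criterion. A control who swaps trial capsules for bought fish oil fails the 80% cut-off, if that refers to capsules. Patients are also questioned at visits, and daily oil-supplement users who will not stop are excluded. A reader might infer that the rule is blind to cross-over altogether; the document does not support that. The gap is the control who takes both.

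Third, the article promises a full statistical analysis plan. What counts as a significant lack of rise for one patient, and how untested patients are handled, can fairly be left to it. The missing arm is different: the article states a rule, and on the article's own facts that rule gives the wrong set.

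**Conclusion.** The point holds in a limited form. As written, every blood-sampled, fully compliant corn-oil patient is non-compliant, and a control who adds bought fish oil to the trial capsules is retained. A fish-oil-only reading removes the first fault but not the second, and adds uneven exclusion.

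Three stronger readings are not supported. The rule does not reject all compliant controls, because only those in the blood subgroup can be classified by it. A bias of 2.5 to 5 points is not the expected size: it ignores the 80% cut-off, which carries no arm restriction, and so is an upper bound under assumed risks. About 0.7 to 1.3 points follows from the milder assumptions above, which are also not in the document. Finally, the trial's main conclusion is not at risk: the intention-to-treat comparison and the sample size do not use this rule, and the per-protocol analysis is run only if cross-over occurs.

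Severity is minor to moderate; it is not a must-fix.

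**What to change.** Define the main per-protocol set by one rule for all patients in both arms: at least 80% of planned capsules by count, saying explicitly that this is what the 80% means. Within the blood-sampled subgroup, apply the erythrocyte measure by arm:

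- fish oil: non-compliant if the EPA plus DHA rise is below a pre-specified cut-off;
- corn oil: contaminated if the rise is above that cut-off.

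Set the cut-off and the arm-specific wording before unblinding, so that results cannot influence who is excluded. Running the analysis whether or not cross-over is seen, or adding an instrumental-variable estimate, would be a matter of preference and is not needed to correct this fault.

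The cost is a few sentences in the analysis plan. Capsule counts and blood samples are already planned.

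### The primary missing-data method depends on a 5% switch that is poorly set against the implied 18.3% dropout margin; one approach should be fixed before unblinding

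*Protocol article*

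**What the plan says.** All of the following is in the protocol article, section Statistical analysis and sample size, unless noted.

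- Planning rates: "we expect an OIPN prevalence of 50% in the control group", and the investigators "estimate a prevalence in the fish oil group to be 23" percent.
- Size: "Using 80% power and 5% risk of type I error", "the sample size estimate is 49+49 patients for the primary objective". The named primary test is a chi-square comparison of two proportions, under intention-to-treat.
- Margin: "To account for dropouts, the project will include 120 patients, with 60 patients in each group". No dropout rate is given.
- Missing data, first branch: "in the case of <5% missing data, analyses will be performed as complete case".
- Missing data, second branch: when more than 5% is missing, or when the missingness hints at bias, "appropriate methods of imputation will be applied depending on the patterns of missingness". No criterion is given for the bias judgement.
- A full analysis plan for each outcome is promised.
- Section Randomization and blinding: "Randomization is carried out automatically 1:1 and stratified to the study site".
- Section Primary endpoint: OIPN requires relevant symptoms plus at least one abnormal result among four tests (vibration, nerve conduction, pinprick, skin biopsy).

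**The concern.** The stated rule lets three things seen in the data decide how the primary endpoint is analysed: how much is missing, in what pattern, and whether someone judges it likely to bias the estimate. The last can override complete case even below 5%.

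The cut-off also sits far below the margin that the same section builds into enrolment. The number 49+49 comes from a chi-square test on observed patients. If losses come anywhere near the margin, that analysis gives way to an imputed one whose method the article leaves to the observed pattern. At stake is whether the primary estimate rests on a method fixed independently of the data.

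**Working it through.** **1. Reproduce the sample size.** Inputs from the protocol: p1 = 0.50, p2 = 0.23, power 80%, alpha 5% (two-sided assumed; one-sided would give 39). Mean rate = 0.365. Pooled formula without continuity correction:

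n = [1.96·√(2·0.365·0.635) + 0.8416·√(0.50·0.50 + 0.23·0.77)]² / 0.27²
= (1.334 + 0.550)² / 0.0729 = 48.7, so 49 per arm.

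This matches the protocol. Power is 80.2% at 49 per arm and 87.7% at 60 per arm with complete data.

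**2. Implied margin.** 120 − 98 = 22; 22/120 = 18.3%. Check: 49/(1 − 0.183) = 60 per arm.

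**3. The switch in patients.** 5% of 120 = 6. Complete case needs at most 5 missing. Exactly 6 missing (5.0%) falls in neither branch, because one is written as below 5% and the other as above. The margin is 22/6 = 3.7 times the cut-off.

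**4. Chance of leaving the complete-case branch.** Binomial, 120 patients, for assumed true missingness:

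| Assumed missingness | P(6 or more missing) |
|---|---|
| 5% | 0.56 |
| 8% | 0.92 |
| 10% | 0.98 |
| 18.3% | >0.9999 |

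**5. Does the handling change the answer?** Illustration at the planning rates, with 49 observed and 11 missing per arm (an assumption). Observed events: 49 × 0.50 = 24.5, taken as 24; 49 × 0.23 = 11.3, taken as 11. Uncorrected chi-square with single fill-in:

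| Handling of the 11 missing per arm | Control | Fish oil | Difference (points) | p |
|---|---|---|---|---|
| Complete case | 24/49 | 11/49 | 26.5 | 0.006 |
| All missing = OIPN | 35/60 | 22/60 | 21.7 | 0.017 |
| All missing = no OIPN | 24/60 | 11/60 | 21.7 | 0.009 |
| Both arms at control rate (5 of 11) | 29/60 | 16/60 | 21.7 | 0.014 |
| Controls 5 of 11, fish oil 7 of 11 | 29/60 | 18/60 | 18.3 | 0.040 |
| Controls 5 of 11, fish oil 8 of 11 | 29/60 | 19/60 | 16.7 | 0.062 |
| Extreme: controls 0 of 11, fish oil 11 of 11 | 24/60 | 22/60 | 3.3 | 0.71 |

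The three common rules keep significance. The reversal needs 8/11 = 73% OIPN among missing fish-oil patients, against 11/49 = 22% among those observed and 50% expected in controls.

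**6. Effect on planned power under the same assumption.** Complete case 80%; all missing = no OIPN about 76%; missing fish-oil patients at the control rate about 70%; all missing = OIPN about 68%.

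**The case against.** The strongest reply is that nothing in the section is false. Both branches are written, and enrolling extra patients is compatible with imputing when data are missing. This stands: a reader might infer that the 5% rule contradicts the dropout allowance, but the text does not support that.

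Second, 18.3% is an inference. It is a planning margin, possibly rounded up, and dropout is not the same as a missing endpoint. Under intention-to-treat, someone who stops the capsules can still attend visit 5, and the endpoint definition settles some cases despite a missing test. This also stands, so 18.3% should not be called the missingness the sponsor expects. The 8% and 10% rows show, however, that the cut-off is likely to be passed well below that figure. The article itself points to sources of loss: patients with verified relapse are withdrawn (Study population and eligibility), and the Discussion names discontinuations as a threat to power.

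Third, a reader might infer that the method will be picked after the results are known. The article does not say so. It promises a full analysis plan and places unblinding after the data analysis, so the method could be fixed, or the patterns examined, blind to arm. Leaving the imputation model to that plan is ordinary practice and is not the complaint. The complaint is the rule that the article does state.

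Fourth, one could claim that the handling decides whether the trial is positive. At the planning rates it does so only under a strongly unfavourable pattern. A smaller observed effect would leave less room, but the documents give no basis for putting a figure on that.

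**Conclusion.** The point holds as a weakness in a stated rule. The amount and pattern of missing data, together with a bias judgement that has no criterion, determine whether the primary analysis is complete case or imputed. The 5% cut-off is poorly chosen beside an implied margin of 18.3%, so the complete-case chi-square behind 49+49 is unlikely to be the analysis that runs: the probability of 6 or more missing is 0.98 at 10% missingness and above 0.9999 at 18.3%.

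The consequence is moderate. At the planning rates with 11 missing per arm, common handling rules give p between 0.009 and 0.017, and significance is lost at 8 of 11 missing fish-oil patients with OIPN (p = 0.062). These figures assume equal losses by arm, single fill-in and observed rates equal to the planning rates; they are scenarios and not forecasts. No stated figure in the protocol is wrong.

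**What to change.** Replace the 5% switch with one primary approach, fixed in the analysis plan before unblinding:

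1. **Derive status before calling it missing.** Under the protocol's own definition, a patient without symptoms has no OIPN, and a patient with symptoms and any abnormal test has OIPN, whatever other tests are absent. Only the remainder is missing.
2. **Impute the remainder** by multiple imputation with a small model: arm, site and a few strong predictors already collected, such as the CIPN20 scores at visits 2 to 4. Avoid a large model fitted separately by arm; with about 11 fish-oil events it risks sparse-data failure.
3. **Compare the arms adjusted for site**, since site is the randomisation stratum and the plain chi-square ignores it.
4. **Report as sensitivity** the complete-case result and a delta (tipping-point) analysis.

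The cost is a change of wording and modest programming. The primary result would then rest on a missing-at-random assumption, which the delta analysis is there to probe. The article reports 15 of 120 patients included, so at that stage the change could be made early.
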